### Participant inclusion and exclusion criteria

All adults over the age of 20 years residing in the Lithgow area are eligible, with no exclusion based on inter-current illness, use of medications or any other aspect of demography or personal history.

### Data collection

The data collection will be identical before and after the intervention and will be exactly the same for every participant. The only exception to this is that eight questions not included in the baseline assessment will be added to the follow up survey to measure social inclusion and to assess the proportion of the population that have been reached by the main components of the intervention program. On each occasion, the assessment will commence with a visit to the study participant by a trained research assistant. Once consent has been obtained, the five components of data collection will be initiated, comprising a questionnaire about participant characteristics, a brief physical examination, a questionnaire evaluating consumer knowledge attitudes and behaviours, a multiple pass 24-hr dietary recall and a spot and 24 hr urine collection. Both questionnaires, the physical examination and the dietary recall are completed at the time of the visit. The urine collection is scheduled for a time within the following 3–10 days and a second dietary recall, administered by telephone, will be scheduled for a random sample.

The *questionnaire* is fully structured and will be administered by a research assistant with all responses based on self-report. The questionnaire records information on socio-demographic variables, vascular disease history and current drug treatments. Participants are asked to provide the names of regular medications; if these are not known the purpose of each medication will be recorded (for example, “blood pressure lowering medication”).

The measurement of *knowledge attitude and behaviours* towards salt is based upon a questionnaire adapted from the World Health Organization/Pan American Health Organization protocol for population level sodium determination [13]. The questionnaire contains nine questions; four related to knowledge of personal consumption, recommended daily intake and possible harmful effects of salt and five assessing attitudes and behaviours to lowering salt intake. The participants answer on a range of different scales such as “rarely, sometimes, often”, “yes, no” and “too much, just the right amount or too little”.

*The physical examination* comprises measurement of body weight (using calibrated Tanita HD-357 portable electronic scales (USA)) and height (using a calibrated portable stadiometer Wedderburn WS-HRP model (Australia)) to the nearest 0.1 kg and 0.1 cm respectively, with body mass index (kg/height(m^2^)) then calculated. Blood pressure is measured using a manual inflation blood pressure monitor (A&D UA-&704) in triplicate, according to the American Heart Association protocol [14].

*The multiple pass 24-hr dietary recall* is used to determine all food and beverages consumed from midnight to midnight on the day before the interview, this method has been described in detail in prior reports [15]. Food model booklets are used to assist with the reporting of quantity and prompts provided by interviewers are used to probe for complete food descriptions, variable recipe ingredients, and food preparation including salt added during cooking and at the table. Dietary data are entered into the nutrient analysis package Foodworks Professional version 7, and analysed using AUSNUT 2007 of Food Standards Australia New Zealand. The food coding guidelines [16] are used to code each food and beverage into major, sub-major and minor food categories.

*A single 24-hr urine collection* will be obtained with the first voided urine upon waking on the day of collection being discarded and participants then collecting all voided urine up to and including the first void the following morning. The times at the beginning and the end of urine collection are recorded. During the morning of the collection period a *single morning spot urine sample* will be obtained by asking participants to collect a sample into a 30 ml container. The volumes of the spot sample and the remainder of the 24 hr urine will be recorded and each will be separately assessed for sodium, potassium, creatinine and iodine. The volume and concentration data for each sample will be combined to derive the 24-hr sodium excretion estimate for each individual. The urinary sodium concentration will be measured by ion-selective electrode with the buffered kinetic Jaffe reaction without deproteinisation used for assay of urine creatinine (Cobas Integra 400). The urinary iodine measurement will be completed by using ammonium persulfate digestion prior to Sandell-Koltoff reaction in a microtitre plate format. Suspected inaccurate urine collections (i.e. urinary creatinine < 4.0 mmol/day for women, or < 6.0 mmol/day for men, or a 24-hr urine collection of < 500 ml for either sex) and extreme outliers for urinary creatinine (> 3 standard deviations from the mean) will be excluded from the primary analysis.

### The salt reduction intervention

The goal of the intervention is to reduce salt consumption amongst adults residing in Lithgow. The means by which this will be achieved is through the application of the Communication for Behavioural Impact framework which utilises an integrated communication model to enact community advocacy and impact [17]. There are five broad components to this approach:

1. *Administrative mobilisation and public advocacy* – for putting salt reduction on the agenda of all doctors and nurses, allied health professional and local government staff via engagement through a series of meetings. The desired outcome is for these professionals to advocate for salt reduction within the community.

2. *Community mobilisation –* Businesses, workplaces and school settings will be engaged through meetings, presentations and the provision of the tools to enact salt reduction.

3. *Advertising* – Local channels of communication including newspapers, social media and radio will be targeted with stories about the program. A series of specific advertising initiatives involving local and social media will be scheduled over the period of the intervention.

4. *Interpersonal communication –* information booths will be established in the two main shopping areas and by door knocking individual homes. The tools will be supplied to support interpersonal communication and engagement across the community. These tools will support one-on-one interactions with the community and enable conversations about the importance of reducing salt consumption as well as providing practical ways to achieve a reduction. (see the ‘key messages for intervention’ subsection).

5. *Point of Service/Sale –* the salt substitute has been made available at local cafes and restaurants for use by consumers. Local bakeries have also been provided with the salt substitute to use in baking. Government buildings, medical centres and pharmacies are also stocked with the salt substitute to enable consumers to obtain and replace the salt substitute at no cost.

### Key messages for the intervention

*The salt substitute* comprises a sea salt blend of 136 mg sodium and 176 mg potassium per serving size (0.8 g). This formula results in 70% less sodium than regular salt while retaining good sensory properties [18].

*FoodSwitch* is a smartphone application which allows users to scan the barcodes of packaged foods, receive colour-coded ratings for four key food components (total fat, saturated fat, sugar and salt) and a list of similar foods that are lower salt healthier choices [19].

### Sample size

The planned sample of 600 individuals with 24-hr urine samples in the baseline and follow-up surveys will provide more than 80% power to detect a difference of 0.7 g/day salt between the mean levels of excretion before and after the intervention. There will be more than 95% power to detect a difference of 1.0 g/day salt or greater.

### Data analysis

The characteristics of the full baseline and follow up samples will be summarised and compared, as will the characteristics of the volunteers, those selected at random and those for which paired baseline and follow-up specimens are available.

For each individual, the 24-hr sodium excretion value (mmol/day) will be calculated as the concentration of sodium in the spot urine (mmol/L), multiplied by the spot urine volume (L/day) added to the concentration of sodium in the remaining urine (mmol/L) multiplied by the volume of the remaining urine (L/day). The conversion from mmol to grams will be made by dividing by 17 and the conversion from sodium (Na) to salt (NaCl) by multiplying by 2.542.

The primary comparison between baseline and follow-up levels of 24-hr urinary sodium excretion will be made using an inverse-variance weighted fixed effect pooled estimate of the effects in the sub-sets of participants. The primary analysis will be supplemented by subsidiary analyses that separately explore the baseline and follow-up differences for 1) the volunteer sample, 2) the random sample and 3) the sample for which both baseline and follow-up specimens are available. Differences will be tested using t-tests and paired t-tests. The analysis will be unadjusted unless there is evidence that the baseline and follow-up samples differ in regard to age, sex or body mass index, in which case these covariates will be included in the models.

Bland-Altman plots will be used to explore the agreement between spot urine and 24-hr urine collections, and to determine whether the agreement between the two methods of collection varies across different levels of sodium excretion.

Daily iodine intake will be estimated by multiplying the concentration of iodine in the urine measured in μg/l by 0.0235 and by body weight measured in kilograms [20]. Urinary iodine status data will be summarised as median urinary iodine excretion values and the proportions with iodine deficiency and iodine sufficiency according to the World Health Organization and the International Committee on the Control of Iodine Deficiency Disorders (ICCIDD) [21]. Mann–Whitney U tests will be used to compare differences in urinary iodine excretion according to World Health Organization urinary salt excretion target of ≥ 5 g/day and < 5 g/day, while general linear models will be used to investigate the continuous association between iodine and sodium excretion.

The level of agreement between dietary sodium assessments and 24-hr urinary sodium assessments will be investigated using Bland-Altman plots. While the associations of knowledge, attitudes and behaviours with 24-hr urinary sodium excretion will be investigated using general linear models.

Throughout, a p-value of 0.05 or less will be taken to indicate a finding unlikely to have arisen solely by chance. No corrections for multiple testing will be implemented. If appropriate, sensitivity analyses will use multiple imputation to cope with missing values.

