## Background

The global burden and threat of non-communicable disease (NCDs) creates a major public health challenge that undermines social and economic development throughout the world [1]*.* In 2008 an estimated 63 per cent (36 million) of all global deaths were due to NCDs, comprising mostly cardiovascular diseases [2]. In Australia, cardiovascular disease is the leading cause of death and disability and the number one cost to the health sector [3,4]. There is clear evidence that a diet high in salt is associated with increased blood pressure, and that increased blood pressure leads to increased risk of vascular diseases [5]. Whilst there is no definitive estimate of population dietary salt intake in Australia, it is widely accepted that average consumption is between 7 and 12 g/day [6]; this is far above the suggested dietary target for Australians of 4 g/day [7].

The reduction of salt intake and sodium content of food has been recommended as a cost effective action that should be undertaken immediately, with expected accelerated results in terms of lives saved, cases of disease prevented and costs avoided [8]. As such, salt reduction activities are being promoted worldwide as a core component of efforts to achieve a 25 per cent reduction in avoidable NCDs by the year 2025. Specifically, the goal is to achieve a 30 per cent reduction in average salt consumption by 2025 [9]. The current Australian approach to reducing population salt intake is based upon voluntary food supply reformulation [10]. Community-based approaches may also be of value, especially those which place strong emphasis on behaviour impact by providing tools that enable the translation of knowledge into behavioural change [11].

In this study, two tools which may assist consumers to reduce salt consumption were identified. The first is a sodium-reduced salt substitute. Not only because a salt substitute might have an important effect on salt intake for individuals using alarge amount of discretionary salt, but also because it offers a talking point for consumers to engage around. The second tool, *“FoodSwitch”*, addresses the primary contributor to salt in the diet; processed foods. This electronic tool empowers consumers to choose healthier, lower salt versions, of food types they enjoy by providing specific advice about which products to pick from the supermarket shelves.

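### The conversion divides mmol of sodium by 17, which already gives grams of salt, then multiplies by 2.542, so urinary salt comes out 2.56 times too high

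*Protocol article*

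**What the plan says.** In Data analysis, sodium concentration times volume is summed over the spot sample and the rest of the collection, which gives 24-hr sodium excretion in mmol/day. The next sentence turns this into mass: "from mmol to grams will be made by dividing by 17 and the conversion from sodium (Na) to salt (NaCl) by multiplying by 2.542". It does not say what substance the grams obtained from the division by 17 refer to, and no other section gives a different conversion.

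Three other statements depend on a correct gram scale or allow it to be checked:

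- Background, on Australian salt intake: "it is widely accepted that average consumption is between 7 and 12 g/day".
- Sample size: "more than 80% power to detect a difference of 0.7 g/day salt between the mean levels of excretion before and after the intervention".
- Data analysis, iodine comparison, which splits participants by the "World Health Organization urinary salt excretion target of ≥ 5 g/day and < 5 g/day".

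**The concern.** The two constants do not belong in one chain. The factor 2.542 is the mass ratio of salt to sodium, so it must act on grams of sodium. The divisor 17 does not produce grams of sodium; it produces grams of salt. An analyst who takes the sentence in order converts to salt twice.

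The primary objective in Study aims is framed as mean salt intake, so the error would reach the headline result: the level before, the level after, and the change with its confidence interval, all in g/day. It would also misplace an absolute cut-off, which a scale error does not leave intact. If the intermediate value is labelled grams of sodium, the planned Bland-Altman comparison of dietary with urinary sodium would show a disagreement produced only by the units.

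**Working it through.** **Inputs.** From Data analysis: sodium in mmol/day, divisor 17, factor 2.542, cut-off 5 g/day. From Background: 7 to 12 g/day. From Sample size: 0.7 g/day. Not in the article, but physical constants: molar mass of sodium 22.99 g/mol and of sodium chloride 58.44 g/mol.

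**1. Can the stated constants be reproduced?**
- Salt per gram of sodium: 58.44 / 22.99 = 2.542. This reproduces.
- mmol per gram of sodium: 1000 / 22.99 = 43.50. The stated 17 does not reproduce as a sodium divisor.
- mmol per gram of salt: 1000 / 58.44 = 17.11. The stated 17 matches this to within 0.7%.
- Cross-check from the article's own constants: 17 × 2.542 = 43.2, close to the sodium divisor of 43.5. The value 17 therefore already contains the sodium-to-salt step.

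**2. Size of the error.**
- Chain as written: 2.542 / 17 = 0.1495 g of salt per mmol.
- Correct: 58.44 / 1000 = 0.0584 g of salt per mmol.
- Ratio: 0.1495 / 0.0584 = 2.56.
- If the result of the division by 17 is called grams of sodium, the ratio is (1/17) / 0.02299 = 2.56 as well.

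**3. Check against the article's own intake range.**

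| True salt (g/day) | Sodium (mmol/day) | mmol / 17 | mmol / 17 × 2.542 |
|---|---|---|---|
| 7 | 119.8 | 7.05 | 17.9 |
| 9 | 154.0 | 9.06 | 23.0 |
| 12 | 205.3 | 12.08 | 30.7 |

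Division by 17 alone returns the stated range almost exactly. The full chain puts it far outside.

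**4. Effect on the change.** A true difference of 0.7 g/day becomes 0.7 × 2.56 = 1.79 g/day.

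**5. Effect on the 5 g/day split.** Under the written chain, 5 g/day is reached at 5 × 17 / 2.542 = 33.4 mmol/day, which is 33.4 / 17.11 = 1.95 g of salt. The correct position is 5 × 17.11 = 85.6 mmol/day. To illustrate, assume that salt excretion is normal with mean 8 to 9 g/day and SD 3 to 3.5 g/day (assumed figures, not in the article):
- True share below 5 g/day: from 9% (mean 9, SD 3, z = −1.33) to 20% (mean 8, SD 3.5, z = −0.86).
- Share classed below 5 g/day by the chain, that is below 1.95 g: from 1% (z = −2.35) to 4% (z = −1.73).

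**6. Effect on the primary test.** A constant factor multiplies each difference and its standard error alike, so the t statistics are unchanged. The inverse-variance weights are all divided by the same number, so the relative weights are unchanged too. The p-value for the pooled change does not move.

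**The case against.** The best defence is that the sentence lists two separate factors rather than a sequence: 17 for urinary mmol to grams of salt, and 2.542 for sodium already in grams, such as that from the dietary recalls. On that reading nothing is inflated and only a label is missing. The text does not support it well. The passage starts from urinary sodium in mmol, joins the two steps in one sentence, and names the second as sodium to salt. It nowhere says that the first step yields salt. Even on this reading, an analyst who wants grams of urinary sodium and divides by 17 is wrong by the same 2.56.

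Several limits on scope do stand:

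- Dietary-recall sodium comes from a food composition database, not from mmol, and is unaffected.
- The null hypothesis concerns sodium excretion, which can be tested in mmol/day, and the test is invariant to the factor in any case.
- Nothing shows that the 0.7 g/day planning difference or its power rests on this conversion. No SD is stated from which to tell.
- The iodine objective is exploratory and concerns women aged 20 to 45, so the percentages below 5 g/day are illustrative and not specific to that group. The shift of the cut-off from 86 to 33 mmol does not depend on them.

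**Conclusion.** The conversion is wrong as written and must be corrected. Applied in the stated order, it overstates every urinary salt value, and every change in g/day, by a factor of 2.56. This rests only on two molar masses and on reading the sentence in sequence, which is its natural sense. The validity of the primary hypothesis test is not in question; its estimate and confidence interval in g/day are. In the iodine analysis the group membership itself changes, so the Mann-Whitney result can change and not only its units.

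A related inconsistency would make the error harder to notice. The Abstract describes the 0.7 g/day target as sodium, while Sample size describes it as salt. Since 0.7 g of sodium is 0.7 × 2.542 = 1.78 g of salt, a double-converted true fall of 0.7 g of salt (1.79 g/day) would look almost the same as meeting the target as the Abstract words it. Whether the analysis code contains the error cannot be determined from the article.

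**What to change.** Replace the conversion sentence with: *Sodium in mmol/day is converted to grams of sodium by dividing by 43.5 (that is, multiplying by 22.99/1000). Grams of sodium are converted to grams of salt by multiplying by 2.542. Equivalently, salt in g/day equals sodium in mmol/day divided by 17.1.*

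Then check the derivation code against one worked value: 154 mmol/day must return 3.54 g of sodium and 9.0 g of salt. Check the 2011 baseline results in the same way, since Project status says that they informed the design of the intervention, along with any baseline figures used in the sample size. In the same edit, make the Abstract and Sample size agree on whether 0.7 g/day is sodium or salt.

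The cost is one sentence and a short code check. No new data are needed.

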**Methods:**

The study comprises a baseline assessment followed by a targeted intervention and then an evaluation of efficacy. The study location is Lithgow, a regional town in New South Wales, Australia. The salt reduction intervention is based upon the Communication for Behavioural Impact framework which utilises an integrated communication model to enact community advocacy and impact by providing tools that enable the translation of knowledge into behavioural change. The duration of the intervention will be between 6 and 12 months. The primary evaluation will be through measurement of 24-hr urinary sodium excretion in independent population samples aged > 20 years, drawn before and after the intervention period. The study is designed to detect a difference in mean sodium excretion of 0.7 grams per day or greater with 80% power and p = 0.05.

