**Figure 1 F1:**
[figure not shown]
Project design.

*For the random sample*, at baseline the electoral roll will be used to obtain the name and address of each potential participant with electronic databases searched to identify corresponding telephone numbers. At follow up a random sample will be selected from the local telephone directory. Potential participants will be first mailed invitations to take part in the survey, with an explanation of the purpose of the study, a participant information sheet and a consent form provided. These individuals will then be contacted by telephone to determine their willingness to participate and to schedule an interview time. Where a telephone number cannot be obtained, the home address will be visited by a member of the research team to determine willingness to participate.

*The volunteer sample* will be recruited by offering participation in the study to individuals at two local shopping centres, workplaces and community events. An information booth will be set up where those interested can seek further information about participation and arrange a visit by a member of the study team.

*Re-sampling of the participants included at baseline* will be done by verifying participants are still residents of Lithgow using electronic databases and then mailing invitations to take part in the follow up survey in the same way that we did for initial sampling.

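### Adjusting for age, sex and BMI only when the two surveys are first shown to differ leaves some avoidable confounding, and gives up a little precision, in the random and volunteer comparisons

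*Protocol article*

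**What the plan says.** The Data analysis section leaves covariates out by default: "analysis will be unadjusted unless there is evidence that the baseline and follow-up samples differ in regard to age, sex or body mass index". Only when such a difference is found does the model change, and the covariates then enter. The section does not define what counts as evidence. The only threshold in the article is the general one, that "a p-value of 0.05 or less will be taken to indicate a finding unlikely to have arisen solely by chance". Nor is it explicit whether a trigger brings in all three covariates or only those that differ.

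The rule feeds the primary result, which is an "inverse-variance weighted fixed effect pooled estimate of the effects in the sub-sets of participants". The accompanying tests are simple: "Differences will be tested using t-tests and paired t-tests".

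The abstract describes "independent population samples aged > 20 years, drawn before and after the intervention period". Under Participant selection and recruitment, the frame for the random sample changes between surveys: "at baseline the electoral roll will be used to obtain the name and address of each potential participant", whereas "At follow up a random sample will be selected from the local telephone directory". Volunteers come from shopping centres, workplaces and community events, and baseline participants are also invited back.

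**The concern.** Nothing in the design makes the two surveys alike in composition. There is no randomisation and no control community is described. People reached through a telephone directory may differ in age and sex from people on an electoral roll.

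A balance test asks whether an observed difference could be chance. The question for the estimate is whether that difference, multiplied by the covariate's effect on salt excretion, moves the before-after contrast. A difference too small to trip the test can still do so, and when the check misses it the imbalance goes straight into the primary estimate. When there is no imbalance, the rule usually leaves out covariates that would have reduced residual variance.

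At stake is a modest shift in the primary estimate and some power, both avoidable with data that the study already plans to collect.

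**Working it through.** **Inputs from the protocol.** More than 80% power for 0.7 g/day salt and more than 95% for 1.0 g/day, with 600 individuals (Sample size); p = 0.05 (Abstract). No SD is given, and 600 can be read as per survey or in total, so both are run.

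**Assumed.** Two-sided testing; trigger at p ≤ 0.05; half of each sample men; age SD 15 years; BMI SD 5 units; effects on salt of 2 g/day for sex, -0.02 g per year of age and 0.1 g per BMI unit.

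**1. The plan's own figure.** The largest SD compatible with the stated power is

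SD = difference / [(z_α/2 + z_power) × √(2/n)].

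- 600 per survey: 0.7 / (2.802 × 0.0577) = 4.33 g/day; for 1.0 g at 95%, 1.0 / (3.605 × 0.0577) = 4.80.
- 300 per survey: 0.7 / (2.802 × 0.0816) = 3.06 g/day; for 1.0 g at 95%, 3.40.

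The two power statements are compatible with each other but cannot be confirmed without the SD.

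**2. What can pass the check.** The largest non-significant imbalance is 1.96 × √(2/n) SD: 0.113 SD with 600 per survey and 0.160 SD with 300. For sex (SD 0.5) that is 5.7 or 8.0 percentage points. If one covariate sits at that limit and carries all the explained variance, the bias is 0.113 × 4.33 × √R² (equally 0.160 × 3.06 × √R²) = 0.49 × √R². That gives 0.11 g/day at R² = 5% and 0.16 at 10%. This is an upper limit for a single missed imbalance, not an average.

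**3. An average scenario.** Variance explained = 2² × 0.25 + 0.02² × 15² + 0.1² × 5² = 1.00 + 0.09 + 0.25 = 1.34. Divided by 3.06² this is 14%; divided by 4.33², 7%. Suppose follow-up has 6 points fewer men, is 2 years older and is 0.5 BMI units lower. The unadjusted bias is (-0.06 × 2) + (2 × -0.02) + (-0.5 × 0.1) = -0.12 - 0.04 - 0.05 = -0.21 g/day.

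**4. Simulated mean bias in this scenario (g/day salt; 4,000 trials per cell).**

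| | 300 per survey, SD 3.06 | 600 per survey, SD 4.33 |
|---|---|---|
| Nothing adjusted under the rule | about 32% of trials | about 8-14% of trials |
| Rule, only differing covariates enter | -0.095 | -0.053 |
| Rule, any trigger brings in all three | -0.044 | -0.008 |
| Always adjusted | about 0 | about 0 |

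Halving all three imbalances keeps the mean bias within the same range, because smaller imbalances trip the trigger less often. The span is therefore about -0.01 to -0.10 g/day: 0.01/0.7 = 1% and 0.10/0.7 = 14% of the target. Type I error under the rule is about 5-6.5%.

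**5. Precision with no imbalance.** With 300 per survey, the SD of the estimate is 0.252 never adjusted, about 0.245 under the rule and 0.232 always adjusted. Against the rule the gain is (0.245 - 0.232)/0.245 = 5%. With R² of 7%, even the gain over never adjusting is only 1 - √(1 - 0.07) = 4%, so the gain over the rule is smaller still. Across the runs the gain over the rule is about 2-6%. The rule is unbiased here.

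**The case against.** The strongest reply is that the rule does catch large imbalances, so what remains is small. That largely stands. On the more natural reading of the sentence, any trigger brings in all three covariates. With 600 per survey the mean bias is then about -0.01 g/day. The scenario also sets all three imbalances to push in the same direction, with covariate effects that are not in the protocol.

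The primary estimator is also pooled and includes a paired sub-set. There sex cancels and everyone ages by about the same amount, which dilutes the bias. An illustration with 200 independent people per survey plus 100 pairs (correlation 0.3-0.5 assumed) gave a pooled bias of about -0.04 g/day.

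Some stronger readings are tempting but not supported:

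- **A bias of 13-14% of the target is what to expect.** It arises only with 300 per survey and only the significant covariates entered.
- **The rule costs an 8% larger standard error, or power of 80% instead of 82-88%.** Those figures compare always adjusting with never adjusting, which is not the plan's rule.
- **Selecting the model from the data makes the test invalid.** With no covariate shift, type I error under the rule was 4.2-4.7%, slightly conservative.
- **The three years of ageing in re-invited participants breaks the rule there.** The trigger is about sample composition, and uniform ageing does not confound a within-person difference.
- **BMI should always be in the primary model.** By the Project status section, the intervention starts in the third quarter of 2013 and follow-up is in the first half of 2014, so follow-up BMI is measured after the intervention has begun.

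None of this is a reason to keep the pre-test. In the scenarios run, always adjusting had less bias when the samples differed and a smaller standard error when they did not.

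**Conclusion.** The concern holds as a modest but avoidable weakness. The protocol fixes a data-triggered adjustment rule for a non-randomised comparison whose sampling frame changes, and nothing else in the article offsets it. It bears on the independent random and volunteer comparisons.

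The size is conditional on the assumed SD, covariate effects and imbalances, on what 600 means, and on which covariates a trigger brings in. A higher R² would give larger figures, and the 600-per-survey reading gives smaller ones. Adjustment also does nothing about secular change between the 2011 and 2014 surveys. The change is worth making because it is almost free, not because the primary result is at serious risk.

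**What to change.** Replace the conditional sentence in Data analysis with:

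> In the independent-sample sub-sets (random and volunteer), the baseline to follow-up difference will be adjusted for age and sex before pooling, regardless of observed balance. The unadjusted estimate, and an estimate further adjusted for BMI, will be reported as sensitivity analyses. The paired sub-set will be analysed by within-person differences.

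The cost is slightly more analysis work. Socio-demographic data, weight and height are already in the data collection. BMI stays out of the primary model because follow-up BMI is measured after the intervention has begun and may be missing for some participants. The planned multiple imputation would not cover that gap in the primary analysis, since it is offered only for sensitivity analyses and only where appropriate.
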